**Methods:**

SCORE is a multicenter, parallel-group, randomized controlled non-inferiority trial enrolling 322 patients aged ≥70 years with acute (≤2 weeks) unstable odontoid Type II, III, or atypical fractures. Participants will be randomized 1:1, stratified by center, to receive surgical stabilization via posterior C1–C2 fixation or conservative management with a rigid cervical collar. The primary outcome measure is the change in Barthel Index (BI) from baseline to 12 weeks. Secondary outcomes include quality of life (EQ-5D), neck pain (Visual Analog Scale, VAS), neck disability (Neck Disability Index, NDI), radiographic fusion, treatment compliance, cross-over rates to surgery, and incidence of adverse and serious adverse events up to 6 months. Follow-ups will take place at 12 weeks and 6 months post-injury, with an additional visit at approximately 2 weeks post-surgery for surgical patients. Analysis will use mixed models for repeated measures, targeting 90% power to detect non-inferiority within a 5-point margin on the BI (one-sided α = 0.025), accounting for 15% attrition.

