### Measures taken (surgical and conservative treatment)

The surgical intervention is a surgical fracture stabilization with a posterior screw-rod system and represents an established surgical treatment according to standard of care for OFs [3,13,14,20,40,41]. The routine surgery commonly lasts approximately 100 minutes and requires a hospital stay of about 6 days [42,43]. An additional external bracing in the postoperative setting is not required. The surgery is tailored specifically towards geriatric insufficiency fractures of the odontoid, which makes stabilization with a screw-rod-construct from a posterior approach a necessity to achieve adequate stability for this patient population. We deliberately exclude the possibility to conduct an anterior fusion by odontoid screw fixation as described by Böhler, which has been shown to be a biomechanically insufficient treatment particularly in geriatric patients [6,15,23,44,45].

The conservative intervention also aims for immobilization, but via an external collar. A typical detriment of the conservative intervention in everyday practice stems from its absolute reliance on the patient’s compliance to wearing the collar permanently for at least 12 weeks, which considerably challenges this treatment strategy [22]. This compliance problem is highly relevant to the treatment outcome, although data on compliance rates in the elderly are fairly scarce [17,44,46]. We are aware that the regularity of wearing the brace cannot be verified with certainty, and in probably the majority of cases the collar is not worn permanently against the physician`s recommendation due to relevant side effects. Therefore, the adherence to therapy will be assessed via a patient diary in which the hours of wearing the collar will be documented. However, this will reflect the everyday reality and belongs to a real-life representation of the conservative therapy regimen.

Over the course of this study, patients of the conservative group can undergo surgical intervention, if requested by the patient or advised by the treating physician, until week 12. Prior to this crossover surgery, patients are required to attend the crossover visit. After surgery, the patients will be invited to Visit 2 at discharge or 14 days post-surgery at the latest, and to Visit 4 at 6 months.

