VAS Neck Pain: A standardized instrument for assessing neck pain on a continuous, visually coded scale that is used in routine clinical practice.

Neck Disability Index (NDI)): A questionnaire used to measure neck-specific disability for both groups, constituting the secondary outcome.

Concomitant medications: Categorized by substance class; antidiabetics, anticoagulants, antithrombotic medicine, antiosteoporotic agents (vitamin D3, calcium, bisphosphonates), medication for movement disorders (e.g. Parkinson’s disease, etc.), antidepressants, steroids, and “other”.

Adverse Events (AEs): Monitoring of all AEs and documentation at each visit, with particular attention to safety-relevant adverse events of special interest (AESIs) and serious adverse events (SAEs).

Duration of Surgery: Time taken to complete the surgery (surgical group or cross-over).

Patient or caregiver diary: diary for patients to document daily duration of cervical collar wearing (conservative group).

Readmission to Hospital: Recording if the patient is readmitted to the hospital any time during the study until week 12, i.e., for the management of medical or surgical complications of either treatment.

Crossover to Surgical Group (see crossover visit): Noting if the patient switches from the conservative to the surgical arm due to failure of conservative treatment until week 12. In case of crossover and conduction of surgery, documentation of visits 1 (surgery), 2 (discharge) and 4 (6 months), after which the study concludes for the crossed patient.

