### Statistical analyses

Analysis will be performed on all patients who were randomized to the study. The primary estimand and its attributes are described in Table 1.

**Table 1 pone.0337999.t001:** Definition of all five attributes used to construct the primary estimand for the SCORE study (non-inferiority setting).

Primary estimand	
**Population**	Geriatric patients with recent type II & III odontoid fractures (as defined by trial inclusion/exclusion criteria).
**Variable**	Functional status accessed as the change in Barthel Index (BI) between baseline and 12 weeks thereafter
**Treatment**	• Surgical stabilization C1-2 by dorsal screw-rod construct (duration of treatment: Approximately 100 min + approximately 6 days hospital stay) or • Conservative therapy by external cervical collar immobilization (duration of treatment: 12 weeks)
**Population-summary measure**	Mean difference, including 95%CI.
**Intercurrent event (IE) and strategy**	• Refusal of therapy as randomized – multiple imputations (hypothetical estimate) • Crossover from the conservative to the surgical arm after randomization but before week 12 – use the last available BI value before surgery as best estimate of the hypothetical BI value at week 12 *Note: Cross-over from the conservative to the surgical arm after week 12 is allowed, as it does not influence the primary variable, which is measured at week 12* • Loss to follow-up after start of therapy – multiple imputations; missing at random assumed • Death – (expected ca. 10%) multiple imputations (hypothetical estimate)

Intercurrent events (IEs) will be dealt with using a hypothetical strategy to determine the treatment effect without the abovementioned IEs.

The primary endpoint will be tested using a mixed model for repeated measures (MMRM) of BI, where treatment, time, their interaction, baseline BI scores, age, and CCI will be fixed covariates, and study center will be a random covariate. In case the model does not converge due to small centers, the covariate center will be abandoned. The adjusted mean difference between groups in the primary outcome will be tested at the 12-week time point.

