### Aims and outcomes of the trial

The principal goal is to assess the functional autonomy of elderly patients. The BI, originally described in 1955, is a 10-item measure of activities of daily living and has been proven to be reliable and precise especially in the elderly [30–36]. It is commonly used as a functional outcome indicator and predictor of disability after traumatic events such as hip fractures [31,33,48]. We specifically chose 12 weeks for the primary outcome to mitigate the rates of loss of follow up and compliance, which is a known issue in this patient population [7,14,15,21,23,44]. To assess the quality of life we will additionally employ the EuroQol 5D. An instrument designed for the disability of patients with conditions of the cervical spine is found in the neck disability index and VAS for chronic neck pain [29]. These instruments are all validated in literature and widely adopted for scientific problems of similar nature [57,58]. The radiographic outcome encompasses the assessment of bony fusion on CT scans obtained at follow-up, which represents standard of care. An important assessor of patient compliance will be the time of wearing the cervical collar per day in hours, which will be recorded in a patient diary by the patients themselves or their authorized caregiver. The number of patients undergoing surgery despite conservative therapy (cross-over rate) will be captured. Adverse events represent a key outcome assessor for both arms, particularly in the in-hospital setting, all adverse events will be assessed during study participation.

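### Crossover surgery is allowed after week 12, but the crossover item as described stops at week 12, so the crossover rate and the 6-month comparisons may be hard to read

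*Protocol article*

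**What the plan says.** Several parts of the protocol article bear on crossover.

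- *Measures taken (surgical and conservative treatment)*: "patients of the conservative group can undergo surgical intervention, if requested by the patient or advised by the treating physician, until week 12". A crossover visit comes first, and Visits 2 and 4 follow the operation.
- *Statistical analyses*, note in Table 1: "Cross-over from the conservative to the surgical arm after week 12 is allowed, as it does not influence the primary variable".
- *Data to be collected*, crossover item: "Noting if the patient switches from the conservative to the surgical arm due to failure of conservative treatment until week 12".
- *Data to be collected*, readmission item: "Recording if the patient is readmitted to the hospital any time during the study until week 12".
- *Data to be collected*, surgery duration: "Time taken to complete the surgery (surgical group or cross-over"), with no end date. Adverse events: "Monitoring of all AEs and documentation at each visit".
- *Aims and outcomes of the trial*: "The number of patients undergoing surgery despite conservative therapy (cross-over rate) will be captured", with no end date.
- Abstract, *Methods*: crossover rates are among the secondary outcomes. The list ends with "incidence of adverse and serious adverse events up to 6 months", and it is not clear whether the 6-month period also applies to crossover.

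The secondary outcomes are compared between groups at 12 weeks and 6 months. A sensitivity analysis of the primary endpoint regroups patients by the treatment they received. It counts conservative patients who crossed over as surgical and gives no cut-off date for the operation. (In the text as read, both statements appear after the ethics paragraphs but belong to the statistical analyses.)

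**The concern.** The treatment section and the Table 1 note give different windows for crossover, and the data item follows the narrower one. A conservative patient operated on in month 4 is permitted to have that surgery, is still in follow-up, and fits the description of the crossover rate in *Aims and outcomes*. The crossover item as worded does not include that patient.

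Surgery soon after week 12 is foreseeable. Collar treatment lasts 12 weeks. CT for fracture healing is done at Visit 3, which by elimination is the 12-week visit. The *Background* says that consequences of conservative treatment, insufficient healing among them, often lead to secondary stabilization. Non-union may therefore be found just when the crossover item closes.

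Three results are at stake: the completeness of the crossover rate, the reading of the 6-month contrasts, and the grouping in the as-treated analysis. In that analysis, a Barthel Index (BI) measured before an operation could be credited to surgery.

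**Working it through.** **1. Where each statement puts the end of the window**

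| Statement | End of window |
|---|---|
| Treatment section, crossover surgery | week 12 |
| Table 1 note, crossover allowed | beyond week 12, no end |
| Crossover data item | week 12 |
| Crossover rate in *Aims and outcomes* | none stated |
| Secondary comparisons | 12 weeks and 6 months |
| As-treated rule | none stated |

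Taking 6 months as 26 weeks, the uncovered stretch is 26 − 12 = 14 weeks, more than half of follow-up.

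**2. The planning figures, for scale**

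Inputs from *Sample size calculation*: margin 5, SD of change 12.7, true difference 0, one-sided α 0.025, 137 evaluable and 161 randomized per arm.

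- Normal approximation: 2 × 12.7² × (1.960 + 1.282)² / 5² = 135.6, so 136 per arm. With the t distribution, power is 89.9% at 136 and 90.1% at 137. The stated 137 is right.
- Drop-out: 274 / 0.85 = 322.4, against 322 stated.
- Planned standard error: 12.7 × √(2/137) = 1.53 BI points.

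Nothing in this point changes these figures.

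**3. If late operations are not counted as crossover**

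The article gives no rate of late surgery, so the counts below are assumptions. The shortfall in a crossover rate counted to month 6, with 161 conservative patients, would be:

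- 1 operation: 1/161 = 0.6 percentage points
- 5 operations: 5/161 = 3.1 percentage points
- 8 operations: 8/161 = 5.0 percentage points

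**4. If late operations are known and the as-treated rule is applied literally**

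Suppose k conservative patients are operated on after the week-12 assessment, and their BI change to week 12 is d points worse than that of the other patients, who do not differ on average between arms. Using simple means without covariates, moving them to the surgical group shifts the contrast by

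k × d × [1/137 + 1/(137 + k)].

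| k | d | Shift (BI points) | Shift / 1.53 |
|---|---|---|---|
| 1 | 1 | 0.015 | 0.01 |
| 1 | 5 | 0.07 | 0.05 |
| 5 | 5 | 0.36 | 0.23 |
| 10 | 5 | 0.71 | 0.46 |

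Both k and d are assumed. If these patients did worse, the shift goes against surgery, which is the conservative direction for non-inferiority.

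For any one patient, steps 3 and 4 are alternatives: an operation nobody knows of cannot be reclassified.

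**The case against.** The strongest reply is that the two windows can be reconciled. The treatment section may describe a managed crossover with its own visit during the 12-week treatment period, while the Table 1 note only explains why later surgery is not an intercurrent event for a 12-week variable. That is coherent, but the article does not say it, and the note uses the word crossover for the later surgery too. On this reading, the period over which the crossover rate is counted is still undefined.

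A reader might infer that late operations will go unrecorded. The documents do not support that. The article condenses a fuller protocol, Figs 1 and 2 and the eCRF are not shown, and *Aims and outcomes* states an intent to capture these operations. Surgery duration and adverse events may also reveal some of them, though neither is described as a crossover record. The readmission cut-off adds little, since that item concerns complications of either treatment. What stands is narrower: the crossover item has an explicit week-12 end, which conflicts with a stated permission and an outcome without a time limit. That is more than missing detail.

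A reader might also infer that the as-treated analysis will misclassify late operations. The sentence most naturally means crossing over later than randomization, and it concerns a 12-week endpoint, so surgery before week 12 may be all that is intended. It sets no such limit, however, and one clause would settle it.

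Finally, no described analysis needs the dates of late crossovers, and the as-randomized 6-month contrasts can be computed without them. That is correct. The dates matter for describing how many conservative patients had been operated on by month 6.

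**Conclusion.** The point holds as a minor inconsistency. The crossover window differs between the treatment section and the Table 1 note, and the crossover item as described leaves out permitted surgery between week 12 and month 6. The crossover rate may therefore be incomplete and the 6-month contrasts harder to interpret. Read literally, the as-treated rule could also count a pre-operative week-12 BI as a surgical outcome.

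The size is unknown. The documents give neither a late-surgery rate nor a week-12 BI for such patients, so the figures above only illustrate scale. Even ten reclassified patients with an assumed 5-point deficit would move the as-treated contrast by 0.71 points against a margin of 5. It would be wrong to conclude that the primary result is at risk from late surgery: the as-randomized 12-week analysis precedes it, and the sample size does not depend on it. If the full protocol or eCRF already records late operations, the capture question falls away and only the wording needs correcting.

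**What to change.** 1. State one crossover rule, in the same terms, in the treatment section, the crossover data item and the Table 1 note.
2. Record any odontoid-fracture surgery in conservative patients, with date and reason, up to the existing 6-month visit. The reason field should cover patient request as well as treatment failure, since the treatment section allows both and the data item names only failure.
3. Report the crossover rate by week 12 and by month 6.
4. In the as-treated sensitivity analysis, count as surgical only patients operated on before the week-12 Barthel assessment.

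The cost is wording and a few eCRF fields at a visit that already exists. Dates are easier to collect prospectively than to reconstruct later in an elderly population that includes patients with dementia.

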## Abstract

**Background:**

Odontoid fractures of the second cervical vertebra commonly affect elderly patients due to osteoporosis and low-energy trauma. Treatment is controversial, with prolonged cervical collar immobilization risking non-union and complications, and surgical C1–C2 stabilization involving higher upfront surgical risks. High-level evidence from randomized controlled trials to guide optimal treatment decisions is lacking. The SCORE study aims to determine whether surgical stabilization is non-inferior to conservative collar management in maintaining functional independence for elderly patients with unstable odontoid fractures.

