### Sample size calculation

Assuming a non-inferiority study design with a one-sided α = 0.025, we set the expected difference in change of BI scores between the two groups to 0. Unnanuntana et al. (2018) show that the minimal clinically important difference (MCID) of the BI in elderly patients after a surgical intervention is 9.8 [48]. Bouwstra et al. (2018), conclude the smallest detectable change in BI in a geriatric nursing home population to be 3.0 [32]. It is common practice to choose a non-inferiority margin for a patient-reported outcome such as the BI, which is lower than the MCID, see Copay et al [49]. Thus, we set the non-inferiority margin to 5, which is closer to the smallest detectable change than to the MCID and therefore more conservative. The standard deviation of the difference in BI between baseline and week 12 was estimated at 12.7 referencing prior work by Unnanuntana et al [48]. Based on these assumptions, a sample size of 137 in each group (274 in total) will have 90% power to reject the null hypothesis of the one-sided 2.5% significance level t-test that the surgical group is inferior to the conservative group in favor of the alternative hypothesis that the surgical group is non-inferior to the conservative group. Assuming a drop-out rate of 15%, a total of 322 patients will need to be included (161 per arm).

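### Deaths are imputed as if the patient had lived, so the primary Barthel Index comparison does not respond to a mortality difference in either direction

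*Protocol article*

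**What the plan says.** Table 1 (Statistical analyses) defines the primary estimand for the change in BI from baseline to 12 weeks. Among the intercurrent events it gives: "Death – (expected ca. 10%) multiple imputations (hypothetical estimate". The sentence below the table applies a hypothetical strategy to all listed events, so the target is the treatment effect had they not occurred. No time horizon is attached to the 10%.

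The further analyses described are an as-treated repeat of the primary analysis, a model with added covariates linked to missingness, and multiple imputation for each outcome at each time point.

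The secondary outcomes in the abstract are EQ-5D, neck pain, NDI, fusion, compliance, and "cross-over rates to surgery, and incidence of adverse and serious adverse events up to 6 months". Aims and outcomes of the trial gives a similar list. Neither names mortality. An independent safety monitoring board (SMB) is in place and may recommend stopping for safety.

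**The concern.** The trial asks whether surgery is non-inferior in keeping elderly patients functionally independent. A patient who dies by week 12 has not kept independence, yet enters the primary comparison with a BI value for a life that did not continue. The Background section itself reports mortality of up to 44% at an average of two years, so death is a central outcome in this population.

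None of the stated further analyses changes this. The as-treated repeat moves patients between arms, and the other two alter how missing values are modelled. None treats death as a bad result. At stake is what the headline conclusion means: a finding of non-inferiority would say nothing about any difference in deaths, whichever arm it favoured.

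**Working it through.** **Inputs from the Sample size calculation section.** The significance level is 0.025, one-sided. True difference: "we set the expected difference in change of BI scores between the two groups to 0". Margin: "we set the non-inferiority margin to 5". Spread: "The standard deviation of the difference in BI between baseline and week 12 was estimated at 12.7". Size and power: "a sample size of 137 in each group (274 in total) will have 90% power". With 15% drop-out the total is 322 (161 per arm). Mortality of about 10% comes from Table 1.

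**The plan's own figure.** Normal approximation: n = 2 × (1.960 + 1.282)² × 12.7² / 5² ≈ 135.6, so 136 per arm. The noncentral t calculation gives 137 (power 90.1%). 274 / 0.85 = 322.4. The stated sample size reproduces.

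**Share of primary values affected.** 0.10 × 322 = 32.2, about 16 per arm, if the 10% refers to week 12. That is two thirds of the drop-out allowance (0.15 × 322 ≈ 48).

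**Response of the primary test to mortality.** Simulation with 161 per arm, no true difference among survivors, SD 12.7, 5% other drop-out and 4,000 runs per scenario. Deaths are unrelated to BI, and analysing the observed survivors stands in for imputation under missing at random. For comparison, each death is scored as a fixed BI loss relative to survivors. The documents give no BI level, so the loss is an assumed range.

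| Deaths, collar vs surgery | P(non-inferior), planned handling | Death = loss of 30 | 50 | 70 | 90 |
|---|---|---|---|---|---|
| 10% vs 10% | about 90% | 83% | 62% | 44% | 31% |
| 8% vs 12% | about 90% | 59% | 26% | 12% | 6% |
| 5% vs 15% | about 90% | 20% | 2% | 0.4% | 0.05% |

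The planned column is flat. The first row shows that counting deaths also costs precision when mortality is equal. Only the fall from row to row reflects a mortality difference.

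**Shift in the mean.** Difference = −(surgical risk − collar risk) × loss. For an assumed 13% vs 7%, with death scored as BI 0 and survivors averaging 50 to 80: −0.06 × 50 = −3.0 and −0.06 × 80 = −4.8, against a margin of 5. With the arms reversed the shifts are +3.0 and +4.8, and the planned analysis shows those no more than the negative ones.

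**What a comparison of deaths can show.** 95% half-width at 10% mortality: 1.96 × √(2 × 0.1 × 0.9 / 161) = 0.066, or 6.6 percentage points. Two-sided 5% power is about 22% for 8% vs 12%, 43% for 7% vs 13% and 85% for 5% vs 15%.

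**Precision of a composite.** SD = √(0.9 × 12.7² + 0.1 × 0.9 × μ²), where μ is the survivors' mean BI. This gives 19.2 at μ = 50 and 26.9 at μ = 80. Half-width with 161 per arm: 1.96 × SD × √(2/161) = 4.2 to 5.9 points.

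**Tipping point.** With 137 observed per arm and an observed difference of 0, the half-width is 1.96 × 12.7 × √(2/137) = 3.0. This leaves 5 − 3.0 = 2.0 points. With 15% imputed and the standard error held fixed, the lower limit reaches the margin when surgical-arm imputations are lowered by 2.0 / 0.15 ≈ 13 points.

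**The case against.** **Deaths are not hidden.** A reader might infer that they disappear from the trial. They do not: serious adverse events to 6 months are a listed secondary outcome, adverse events are described as a key measure for both arms, and the SMB watches safety. This stands. The point concerns what the primary conclusion can reflect, not whether deaths are recorded.

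**The direction is not known.** A reader might infer that the handling favours surgery, since the abstract speaks of "surgical C1–C2 stabilization involving higher upfront surgical risks". The documents do not support that. The same sentence gives collar treatment its own complications, Background and rationale ties mortality to comorbidity and immobilisation whatever the treatment, and the Discussion reports a slight trend towards surgery. No mortality by arm is given. The insensitivity runs both ways.

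**Part of this is omission from a condensed article.** The secondary outcome list is not presented as exhaustive, and tipping-point or supplementary analyses may sit in documents not shown. Their absence alone would be no finding. What remains is the stated strategy for death, which an analysis plan following Table 1 would carry forward.

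**The remedies are imprecise.** A mortality risk difference has the same 6.6-point half-width as a safety table. In the 13% vs 7% example the composite intervals would be about −7.2 to 1.2 and −10.7 to 1.1, both including zero. At SD 26.9 the half-width of 5.9 exceeds the margin even with an observed difference of 0. This stands, and it is why these analyses can inform the reading of the primary result but cannot decide it.

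**Conclusion.** The point holds as a limit on what the primary result means. Under Table 1 as written, the probability of declaring non-inferiority stays near 90% for every mortality split examined, while analyses that count death as a loss of function respond strongly. Up to about 32 of 322 primary values are concerned.

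This rests on several assumptions: that the 10% refers to week 12 (with a 6-month horizon fewer values are affected); the illustrative mortality splits; a BI loss of 30 to 90 points, or a survivor mean of 50 to 80; and imputation close to missing at random, since the imputation model is not described.

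A reader might go further and conclude that the primary estimand must be replaced, or that the claim should be barred whenever a composite points to harm. Neither follows. Making the composite primary would need a total of about 404 to 1,548 patients (losses of 30 to 90 points, 5% other drop-out). A veto without a threshold would change the decision rule and its power in an undefined way. The change should be made as a cheap improvement; the design does not fail without it.

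**What to change.** Keep the primary estimand and the sample size of 322. Then:

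- Name all-cause mortality at 12 weeks and 6 months, by randomised arm, as a secondary outcome, with risk difference and 95% CI, reported beside the primary result.
- Pre-specify one supplementary analysis of the primary endpoint in which death counts as an unfavourable outcome (BI 0 or worst rank).
- Pre-specify a delta-adjusted tipping-point analysis of the imputed values.
- State that the non-inferiority conclusion will be interpreted together with these results, without a veto rule.
- State the time horizon of the expected 10%.

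The cost is wording and analysis time, since deaths are already collected. The downside is precision: the composite SD is about 19 to 27 instead of 12.7, so that analysis is supportive only and is not powered for the 5-point margin. The choices should be fixed before outcome data are seen by arm.
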